### Sample characteristics

The study will be conducted at Skåne University Hospital serving the towns of Malmö and Lund in southern Sweden. The hospital is a tertiary centre for orthopaedic trauma and an academic centre for orthopaedic research. The hospital serves a defined geographic catchment area, with no other hospital that treats olecranon fractures in that area. Patients referred with olecranon fractures from other hospitals, for example due to severe soft-tissue injury or multi-trauma, will not be eligible for inclusion. To further characterize the study sample, descriptive statistics on age, gender, dominant hand, Mayo subclass (2a or 2b), high energy trauma, and current smoking (during the last month) will be recorded at inclusion or in the peri-operative period.

### Sample size

The primary outcome measure of the study is reoperation rates, and the sample size is based on this metric. Reoperation rates are assumed to be 13% for CF and 27% for TBW, based on a previous study at our institution [16]. As active patient participation is not required to calculate reoperation rates, and as it will be collected in the same health-care system as the previous retrospective study, we do not expect any drop-out of participants (relative to that study) for assessment of reoperations. The sample size of each arm needed to achieve 80% power is 98; thus, we plan to recruit a total of 200 participants, yielding 81% power.

We expect all 200 participants to be available for analyses of peri-operatively recorded variables (age, sex, fracture type, fluoroscopy DAP, fluoroscopy time and operation time). For analyses of complications, the same assumption is made as for reoperations, i.e. no drop-out relative to our previous retrospective study. For all other variables collected at follow-up, we expect 170 participants to be available for statistical analysis. The expected power for all variables at different sample sizes are shown in Table 1, including all relevant assumptions made.

**Table 1 Tab1:** Statistical power and sample size requirements for study outcomes

	**Power *****n***** = 200**	**Power *****n***** = 170**	***n***** needed for 80% power**	**MDD *****n***** = 100**	**MDD**	**MDD *****n***** = 170**	**MDD**	**x̄ or proportion**	**SD**	**MCID**
**Primary measure**										
Reoperation rate (yes/no)	81%	75%	196	0.2	0.16	0.15	0.14	13% vs 27%^a^	-	-
**Secondary measures**										
Complication rate (yes/no)	> 99%	99%	68	0.22	0.18	0.16	0.15	18% vs 45%^a^	-	-
Severe complication rate (yes/no)	81%	75%	196	0.2	0.16	0.15	0.14	13% vs 27%^a^	-	-
* Quick*DASH (score)	94%	89%	138	12.9	10.5	9.9	9.1	13^c^	22^d^	14^e^
Patient satisfaction (VAS)	> 99%	> 99%	36	1.2	1	0.9	0.8	5^b^	2^b^	2^b^
Pain at rest (VAS)	94%	89%	138	1.2	1	0.9	0.8	1^b^	2^b^	1^b^
Pain in motion (VAS)	94%	89%	138	1.2	1	0.9	0.8	2^b^	2^b^	1^b^
bSMFA (score)	94%	89%	138	10.5	8.6	8.2	7.4	27^f^	18^f^	9^g^
dSMFA (score)	94%	89%	138	10.5	8.6	8.2	7.4	30^f^	18^f^	9^g^
**Tertiary measures**										
ROM, flexion (degrees)	> 99%	> 99%	18	4.1	3.3	3.1	2.9	146^h^	7^h^	10^b^
ROM, extension (degrees)	> 99%	> 99%	10	2.9	2.4	2.2	2.1	− 3^h^	5^h^	10^b^
ROM, supination (degrees)	> 99%	> 99%	14	3.5	2.9	2.7	2.5	80^h^	6^h^	10^b^
ROM, pronation (degrees)	> 99%	> 99%	18	4.1	3.3	3.1	2.9	87^h^	7^h^	10^b^
Grip strength (newton)	43%	31%	352	9.4	7.6	7.2	6.6	32^i^	16^i^	5 ^j^
Post-operative antibiotics (yes/no)	< 1%	< 1%	6296	16%	13%	12%	11%	8%^a^	-	2%^b^
Secondary nonunion (yes/no)	< 1%	< 1%	9782	< 0.1%	< 0.1%	< 0.1%	< 0.1%	1%^k^	-	0.5%^b^
Sick leave (days)	< 1%^n^	< 1%^l^	30,790	18	14	13	12	35^b^	302	12
Fluoroscopy time (seconds)	< 1%	< 1%	3024	55	45	42	39	81^m^	94^m^	10^b^
Fluoroscopy DAP (mGy·cm^2^)	< 1%	< 1%	1492	19	16	15	14	25^m^	33^m^	5^b^
Operation time (minutes)	< 1%	< 1%	998	15	13	12	11	83^m^	27^m^	5^b^

Calculations of power and sample size requirements (n) for all outcome measures, including underlying assumptions. Previously published Minimally Clinically Important Differences (MCID) are given for outcomes where non-inferiority testing is performed and are used as non-inferiority margins in statistical analyses

^a^Based on a previous study at our institution [16]

^b^Based on estimations by the authors

^c^Based on QuickDASH following TBW [31]

^d^Based on unpublished data from a previous study where standard deviation (SD) was 22 for CF and TBW, although the sample was small

^e^Ranging from 3.5 to 19 points in the literature with a mean of 14 points [32–36]

^f^Based on outcomes following distal radius fractures as no elbow specific data was found in the literature [37]

^g^To our knowledge, no studies have reported MCID of SMFA following surgery for upper extremity injuries. The MCID was estimated to be half the standard deviation [38]

^h^Based on normal ROM [39]

^i^Based on data on elbow fractures [40]

^j^Based on a review of MCID of grip strength [41]

^k^Based on a study on the outcome of 196 olecranon fractures [42]

^l^Power if *n* = 100 and *n* = 85 as we expect half of the participant to work

^m^Based on data from all CF and TBW cases at our department during 2020

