The tertiary outcome measures are:Grip strength will be evaluated using a JAMAR dynamometer according to the guidelines from the Swedish national quality register for hand surgery (HAKIR) [30]. The dynamometers used will be calibrated at least once every year.Active postoperative range of motion (ROM) for extension, flexion, pronation and supination will be evaluated using the HAKIR guidelines [30].Secondary dislocation and/or nonunion rate will be assessed with a lateral view radiograph 6 months after the operation. In order to minimize radiation dose, only one radiograph and one view will be obtained. If secondary dislocation and/or nonunion is found, the participant will be referred to the standard healthcare system, and further investigation may include a full radiographic examination. Any demonstrated secondary dislocation and/or nonunion is regarded as a complication.Sick leave related to the elbow injury, counted in days.Intra-operative fluoroscopy radiation level will be measured as the dose area product (DAP) in mGy·cm^2^, and intraoperative fluoroscopy time will be measured in seconds. This will be recorded at the time of surgery from the fluoroscopy machine used. The model and make of the machine vary between operating rooms and may change during the study.Surgical time will be recorded in minutes during surgery counting from skin incision to the final suture of the surgical wound.Post-operative antibiotic treatment is defined as any prescribed antibiotic treatment related to the surgery after the intervention.

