### Statistical analysis

For power and sample size calculations, the alpha value was set to 0.05. Our hypothesis is that CF will yield lower reoperation and complication rates, lower intra-operative radiation, and less intra-operative fluoroscopy time; thus, one-sided tests of proportions were used for sample size requirements calculations [47]. For all other variables, tests for non-inferiority were used with assumed means for ratio scalar and interval variables and assumed proportions for nominal variables [47].

Statistical power and sample size requirements for demonstrating clinically significant differences between the groups were calculated using minimal clinically important difference (MCID) values from the literature. Power and sample size data, including relevant assumptions for all calculations, are presented in Table 1.

We expect ≥ 80% power for reoperation rates, complication rates, severe complication rates, *Quick*DASH, SMFA, patient satisfaction, pain in motion and at rest, and ROM. However, we do not expect to achieve 80% power for analysis of grip strength, postoperative antibiotics use, secondary dislocation or nonunion rate, sick-leave time, fluoroscopy time, fluoroscopy DAP, or operation time (Table 1).

The minimal detectable differences (MDD) for various outcomes and study sizes are presented in Table 1. For some of the secondary and tertiary outcome measures, the MDD is smaller than the MCID meaning that the study is under-powered for proving non-inferiority between the groups. Early termination of the trial resulting in a smaller sample size would further reduce MDD, hampering the power of the study.

The final study groups consist of all participants that complete the follow-up and participants that withdraw but permit analysis; see the section “ Post-inclusion withdrawals and exclusions”. The study groups will be compared using the chi-squared test for categorical variables (reoperation, complication) and Student’s *t*-test for continuous variables.

Comparisons between the study groups will primarily be performed by “intention to treat” analyses. If large cross-over between study groups occurs, “as treated” analyses will be performed as well. Subgroup analysis stratified by Mayo classification, age, gender, open fracture, and high energy trauma is planned for all outcomes.

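### Table 1 states the grip-strength mean (32), SD (16) and non-inferiority margin (5) in newtons, a unit that does not fit those figures

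*Protocol article*

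**What the plan says.** Among the tertiary measures in Table 1 is the row "Grip strength (newton)". It gives a mean of 32, an SD of 16 and an MCID of 5, with power of 43% at n = 200 and 31% at n = 170, 352 participants needed for 80% power, and minimal detectable differences (MDD) of 9.4, 7.6, 7.2 and 6.6. The footnotes attribute the mean and SD to a cited study ("Based on data on elbow fractures [40]") and the MCID to a cited review ("Based on a review of MCID of grip strength [41]"). The legend says that the tabulated MCIDs "are used as non-inferiority margins in statistical analyses".

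The outcome definition under Objectives and outcome measures reads "Grip strength will be evaluated using a JAMAR dynamometer according to the guidelines" of the national hand-surgery register. It gives no unit. The newton label in Table 1 is the only unit given for grip strength anywhere in the article.

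**The concern.** A force of 32 N is about 3.3 kgf. As an average grip for a trial population aged 18 and over, from which patients suited to non-operative care (for example the frail) are excluded, that is not physically credible. The same conversion makes the margin 0.51 kgf.

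The margin is a decision threshold, so its unit matters more than a descriptive label would. If grip data are held in newtons and compared with 5, the analysis would almost certainly fail to show non-inferiority of cerclage fixation even if the two methods were identical. If instead someone changes the unit silently at analysis, the margin is altered several-fold after data collection with nothing in the protocol to support it.

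**Working it through.** **Inputs.** From Table 1: mean 32, SD 16, margin 5. From Statistical analysis: "the alpha value was set to 0.05", with non-inferiority tests for outcomes of this type. From Trial summary: 1:1 allocation, so n = 200 and n = 170 mean 100 and 85 per arm. Conversions: 1 kgf = 9.807 N; 1 lbf = 4.448 N. Normal approximations are used throughout, with z(0.95) = 1.645, z(0.90) = 1.282 and z(0.80) = 0.842.

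**1. Reproduce the plan's figures.** They match a two one-sided tests (equivalence) calculation.
- Sample size per arm = 2 × [16 × (1.645 + 1.282) / 5]² ≈ 175.4, rounded up to 176. The total is 352, as stated.
- Power = 2Φ(5 / (16√(2/n)) − 1.645) − 1. At 100 per arm this is 2Φ(2.210 − 1.645) − 1 = 42.8%. At 85 per arm it is 30.5%. The table has 43% and 31%.
- MDD = 16 × √(2/n) × 2.926. Totals of 100, 150, 170 and 200 give 9.36, 7.65, 7.18 and 6.62, as tabulated.

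Only SD/margin = 16/5 = 3.2 enters sample size and power. Multiplying both by any conversion factor leaves 352, 43% and 31% unchanged, so these figures neither reveal the unit nor are harmed by the label.

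**2. Read the row literally.**
- Mean: 32 / 9.807 = 3.26 kgf.
- SD: 16 / 9.807 = 1.63 kgf.
- Margin: 5 / 9.807 = 0.51 kgf.
- Mean plus two SDs: 64 N, or about 6.5 kgf.

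On this reading nearly every participant would grip below 6.5 kgf.

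**3. Size of the discrepancy under each assumed unit.**

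| Assumed unit of 32 / 16 / 5 | Mean, SD, margin in N | Written margin ÷ intended margin |
|---|---|---|
| kgf | 314, 157, 49 | 1/9.8 = 0.102 |
| lbf | 142, 71, 22 | 1/4.4 = 0.225 |

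**4. Consequence if data in newtons met a literal margin of 5.** The test is one-sided non-inferiority at 0.05 with a true difference of zero. Power = Φ(5 / (SD√(2/n)) − 1.645), and n per arm = 2 × [SD × (1.645 + 0.842) / 5]².
- Kilogram assumption (SD 156.9 N), 100 per arm: Φ(0.225 − 1.645) = 7.8%. At 85 per arm it is 7.5%. About 24,350 participants in total would be needed for 80% power.
- Pound assumption (SD 71.2 N), 100 per arm: Φ(0.497 − 1.645) = 12.5%. At 85 per arm it is 11.8%. About 5,010 participants would be needed.

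The like-for-like comparator is the same test with SD and margin in one unit: Φ(2.210 − 1.645) = 71% at 100 per arm, with 254 participants for 80% power. The tabulated 43% and 352 belong to the equivalence calculation and should not be set against these figures.

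**The case against.** The strongest reply is that this is a slip in a label and nothing more. Every calculated figure in the row reproduces, and correcting the unit moves no sample size or power. Grip strength is tertiary, does not drive the sample size or the stopping criteria, and is one of the outcomes for which the protocol does not expect 80% power. The harm also needs two conditions: data held in newtons, and a literal 5 applied to them. A team whose readings centre near 32 with an SD near 16 would naturally apply 5 on that scale and obtain the intended test. All of this stands, and it keeps the point minor.

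A reader might infer more than the documents support:
- **That the figures make sense only in kilograms, so the margin is wrong by exactly 9.81.** Kilograms are never given for this outcome, the two sources are not shown, and the power calculation is scale-free. Kilograms-force is the likeliest reading, but it remains an assumption.
- **That units will be mixed at data entry.** Nothing suggests this. The trial runs at one hospital under one measurement guideline, and the data-entry field is not shown.
- **That the row's arithmetic is wrong.** It is not.

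What the reply does not remove is that a threshold designated for analysis carries a unit that cannot be right for it. Weak grip soon after surgery does not rescue the label either: grip is measured out to 36 months, and the table gives a single mean and a single margin.

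**Conclusion.** The point holds as a unit error in a prespecified margin for one tertiary outcome. The newton label does not fit a mean of 32; that is a judgement of physical plausibility, not a figure from the protocol. The written margin is between about 1/9.8 (kilograms-force, most likely) and about 1/4.4 (pounds-force) of the one intended. Taken literally on newton data, it would cut one-sided non-inferiority power at n = 200 from 71% to somewhere between 8% and 13%. This rests on identical arms, a one-sided alpha of 0.05 and the table's SD converted from the assumed unit. The tabulated sample size and power are unaffected, the MDDs need only the correct unit, and no primary or secondary outcome is touched.

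**What to change.** Before any analysis, look up the unit used in the two sources cited for this row ([40] for the mean and SD, [41] for the MCID). Confirm that both use the same unit, or convert one. Then correct the Table 1 label so that mean, SD, MDDs and margin share that unit, and analyse grip strength in it. Do not convert the row to newtons on the kilogram assumption before that check: if a source used pounds, the conversion would bring in a new error.

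The cost is one look-up and a corrected table entry, recorded through the amendment route the protocol already describes. If the sources share a unit, sample size and power stay as printed. Follow-up is expected to run to 2030, so there is time to do this before the final comparison.

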### Follow-up

After surgery, follow-up will be identical in both study groups (Table 2). Standard peri-operative care will be given at the hospital.

**Table 2 Tab2:** Time-points for follow-up and data gathering, SPIRIT-figure

Activity	− 0.5 to 0	0	0.5	1.5	3	6	12	36
Inclusion, allocation, and randomization	x							
Intervention, both arms	x							
Primary outcome measures								
Reoperation rate				x	x		x	x
Secondary outcome measures								
Complication rate				x	x		x	x
Severe complication rate				x	x		x	x
QuickDASH				x	x		x	x
Patient satisfaction				x	x		x	x
Pain at rest				x	x		x	x
Pain in motion				x	x		x	x
SMFA		x					x	
Tertiary outcome measures								
ROM, flexion			x	x	x		x	x
Grip strength			x	x	x		x	x
Post-operative antibiotics				x	x		x	x
Secondary non union^a^			(x)	(x)	(x)	x	(x)	(x)
Sick leave				x	x		x	x
Fluoroscopy time		x						
Fluoroscopy DAP		x						
Operation time		x						

^a^The secondary dislocation or nonunion rate will be assessed from a lateral elbow radiograph at 6 months or will be recorded if diagnosed at any other time-point

In addition to descriptive baseline data, operation time, fluoroscopy DAP, and fluoroscopy time will be recorded. SMFA-questionnaires will be administered and collected by The Swedish Fracture Register (SFR) by mail shortly after the trauma (recall of pre-injury status), and 12 months later, and this data will be retrieved from SFR by the study officials.

At 2 weeks post-operatively, the cast will be removed, and a physiotherapist will record grip strength and ROM. Any reoperations, complications, ROM, grip strength, and return to work will be recorded at 6 weeks, 3 months, 12 months, and 36 months at the outpatient clinic at the dept. of Orthopaedics by a physiotherapist. PROMs (except SMFA) will be recorded by the participants in REDCap at the same time points. Reoperations and complications are recorded in each patient’s medical journal and subsequently retrieved by the study officials at interim analysis points and at the end of the trial.

At 6 months, a lateral view radiograph will be assessed by researchers DW and GC for any secondary dislocation or non-union. If secondary dislocation or nonunion is confirmed at any other point during the study, it will be recorded.

Any issue requiring additional follow-up or treatment will be handled in the standard health-care system which is public and tax-financed. After 36 months, the current follow-up will end.

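### Table 1 takes the range-of-motion SDs from normal elbows although the outcome is postoperative, so the stated sample sizes and detectable differences are probably too favourable and the ROM power claims are unsupported

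*Protocol article*

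**What the plan says.** The tertiary outcomes under Objectives and outcome measures include ROM in four movements: "Active postoperative range of motion (ROM) for extension, flexion, pronation and supination will be evaluated using the HAKIR guidelines". The Follow-up section sets the first measurement at cast removal: "At 2 weeks post-operatively, the cast will be removed, and a physiotherapist will record grip strength and ROM". Further measurements follow at 6 weeks and at 3, 12 and 36 months.

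Table 1 gives these ROM entries:

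| Movement | Mean | SD | Margin | n for 80% power | MDD, n = 170 | MDD, last column |
|---|---|---|---|---|---|---|
| Flexion | 146 | 7 | 10 | 18 | 3.1 | 2.9 |
| Extension | −3 | 5 | 10 | 10 | 2.2 | 2.1 |
| Supination | 80 | 6 | 10 | 14 | 2.7 | 2.5 |
| Pronation | 87 | 7 | 10 | 18 | 3.1 | 2.9 |

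MDD is the minimal detectable difference, in degrees. Power is given as above 99% at both n = 200 and n = 170. The means and SDs carry footnote h, "Based on normal ROM [39". The 10-degree margin carries footnote b, "Based on estimations by the authors", and the table note says that the MCID values "are used as non-inferiority margins in statistical analyses".

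The Statistical analysis section then lists the outcomes expected to reach at least 80% power. The list ends with "patient satisfaction, pain in motion and at rest, and ROM".

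**The concern.** The SD in a power calculation should describe the patients who will be measured. Variation between operated elbows includes differences in stiffness and recovery after injury, surgery and splinting. A normal-elbow SD leaves these out. Read literally, a flexion mean of 146 with SD 7 puts about 97.5% of patients above 132 degrees (146 − 1.96 × 7 = 132.3) if values are roughly normal. The table names no visit, so this would apply on the day the cast is removed as well. Nothing in the protocol supports that.

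Several other rows of Table 1 use data from injured or operated patients. Grip strength comes from elbow fractures (footnote i), the QuickDASH SD from cerclage and tension-band patients (footnote d), and the fluoroscopy and operation times from the department's own cases (footnote m). SMFA borrows from distal radius fractures and says why (footnote f). Footnote h names its source and gives no reason.

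At stake is how a reader judges the ROM comparison. Table 1 presents a resolution of 2 to 3 degrees, and a requirement of fewer than 20 patients, as properties of this trial.

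**Working it through.** **Inputs.** SDs of 7, 5, 6 and 7 degrees and a margin of 10 degrees (Table 1). Alpha: "For power and sample size calculations, the alpha value was set to 0.05". Allocation is 1:1. The Sample size section expects 170 analysable participants for follow-up variables, that is 85 per arm. The true difference is taken as 0.

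**Step 1: reproduce the table.** All four rows match a two-one-sided-tests (equivalence) form with a normal approximation:

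- n per arm = 2 × [SD × (1.645 + 1.282) / 10]², rounded up
- SD 7: 2 × (0.7 × 2.926)² = 8.4, so 9 per arm, total 18
- SD 6: 6.2, so 7 per arm, total 14
- SD 5: 4.3, so 5 per arm, total 10

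MDD = SD × √(2 / n per arm) × 2.926. With 85 per arm this is SD × 0.449, giving 3.14, 2.24, 2.69 and 3.14 degrees. With 100 per arm it is SD × 0.414, giving 2.90, 2.07, 2.48 and 2.90. These match the n = 170 column and the last MDD column (its heading has lost its sample size; the values fit n = 200). Power is effectively 100% in every row, as stated.

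The same form reproduces grip strength (n = 352; 43% and 31%) and SMFA (n = 138; 94% and 89%). A plain one-sided 0.05 non-inferiority formula gives totals of 14, 8, 10 and 14 for the ROM rows, so the form used is the more conservative one. The arithmetic is right.

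**Step 2: what drives the figures.** Only the SD and the margin enter. The means (146, −3, 80, 87) play no part. Required n scales with SD² and MDD scales with SD.

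**Step 3: vary the SD.** The document gives no postoperative SD, so these values are assumptions. The formula is that of Step 1, and power = 2Φ(10 / (SD × √(2/85)) − 1.645) − 1.

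| Assumed SD | Total n for 80% | MDD at n = 170 | Power at n = 170 |
|---|---|---|---|
| 10 | 36 | 4.5 | > 99% |
| 15 | 78 | 6.7 | 99% |
| 20 | 138 | 9.0 | 89% |
| 25 | 216 | 11.2 | 66% |

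Example at SD 20: 10 / (20 × 0.1534) = 3.260; 3.260 − 1.645 = 1.615; Φ = 0.9468; power = 2 × 0.9468 − 1 = 0.894. At SD 25 the plain one-sided non-inferiority formula gives 83% instead of 66%.

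**Step 4: how large the SD can be before the power claims fail, at n = 170.**

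- Table's form, 80%: 10 / (0.1534 × 2.926) = 22.3 degrees
- Table's form, 99%: 10 / (0.1534 × 4.221) = 15.4 degrees
- Plain one-sided non-inferiority: 26.2 degrees for 80% and 16.4 degrees for 99%

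**The case against.** The strongest reply is that nothing has been miscalculated. The source is disclosed, the figures follow from it, and proxy inputs occur elsewhere in Table 1: satisfaction and pain use the authors' own estimates, and SMFA uses another fracture. ROM is tertiary, and the trial is sized on reoperations alone. The non-inferiority margin is 10 degrees, so a larger MDD affects that conclusion only as it approaches 10, which happens at an SD of about 22. All of this stands, and it keeps the point small.

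A reader might go further and infer that the power figures for ROM are false. The documents do not support that. The SD would have to exceed about 15 degrees, more than twice the largest tabulated value, before power at n = 170 fell below 99%. It would have to exceed about 22 degrees, roughly three times that value, before power fell below 80%. Under the non-inferiority test that the Statistical analysis section describes, the limits are about 16 and 26. No figure in the document shows that any of these limits is passed.

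The objection does not rescue the required n and the MDD. These have no such slack, because they move directly with the SD. Doubling the tabulated SDs to 10–14 degrees raises n from 10–18 to 36–68, and the MDD at n = 170 from 2.2–3.1 to 4.5–6.3 degrees. Disclosing the source does not explain why healthy elbows should stand in for operated ones.

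**Conclusion.** The point holds as a wrong-population input. The required totals of 10 to 18 and the detectable differences of 2.2 to 3.1 degrees (n = 170) or 2.1 to 2.9 degrees (n = 200) describe normal elbows and are probably too favourable for this trial. By how much cannot be settled from the document. Over an assumed SD of 10 to 25 degrees, the total ranges from 36 to 216 and the MDD at n = 170 from 4.5 to 11.2 degrees.

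The power claims, above 99% in Table 1 and at least 80% in the Statistical analysis section, lack support but are not shown to be wrong. The direction of the error rests on the judgement that ROM varies more after injury and surgery than in normal joints. The sizes rest on the table's formula and its 10-degree margin, both taken as given. The matter is minor: a tertiary outcome, with no effect on the trial's size.

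**What to change.** In the four ROM rows of Table 1, replace the SDs with a postoperative value if the authors have one, name its source and visit, and recompute n, power and MDD. If they have none, show the three quantities over an SD range such as 10 to 25 degrees, as in the second table of the working. In the Statistical analysis section, state the SD on which the ROM power claim depends. If the table's formula is kept, that means saying that at least 80% power at n = 170 requires an SD of no more than about 22 degrees.

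New means are not needed for the calculation. The source cited for grip strength should not be assumed to report ROM.

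The cost is four recalculated rows and one sentence. The stated figures for a tertiary outcome become less favourable; recruitment, follow-up and analysis stay as they are.
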